#### Missing data

If any statistical method is needed to account for missing data, multiple imputations will be used. If necessary, professional help with the statistical evaluation is sought (Fig. 1).

**Fig. 1 Fig1:**
[figure not shown]
PROPPER trial flow chart

### Follow-up and data management

Data collected during the hospital stay consists of the primary endpoint DGE rate as well as the secondary outcomes postoperative complication rates, in-hospital mortality, events during gastroscopy, length of ICU and hospital stay. All patients will be monitored for a follow-up period of 5 years. The follow-up intervals in the outpatient clinic will be 30 days, 3 months, 6 months, and 9 months in the first year, followed by biannual visits. Postoperative pain evaluation and quality of life scores will be collected preoperatively, 1 month, 6 months, and up to 5 years postoperatively. Postoperative pain will be assessed daily during hospitalization. All adverse events will be registered and collected in a patient file. All reports, collected data, processes, and administration forms will be encrypted by a coded identification number (ID) to maintain participant confidentiality. The coding list for potential decryption can exclusively be accessed by the study coordinator and the principal investigator. The local database will be secured by a password-protected access system. All files concerning participants (containing names or other personal identifiers) will be stored in a separate locked file in an area with limited access. All data between centers involved in the study will be pseudonymized. All data will be archived for 10 years after the end of the study. An internal audit of the study will be carried out annually in the study center. Table 2 shows the time schedule of enrollment, interventions, and assessments.

**Table 2 Tab2:** Schedule of enrollment, interventions, and assessments

Timepoint	Study period						
	Screening/allocation	Post-allocation					End of FU
	D − 1: Outpatient clinic visit	D0: 1 day pre OP	D1: hospital discharge	Hospital discharge	D30: 30 day post OP	D90: 3-month post OP	5 years
**Enrollment:**							
Eligibility screen	X						
Informed consent	X						
Allocation	X						
**Interventions:**							
Gastroscopy without EPBD		X					
Gastroscopy with EPBD		X					
**Assessment:**							
Baseline characteristics	X						
DGE (primary outcome)			X	X	X	X	
Secondary outcomes^a^			X	X	X	X	
QoL Questionnaire	X		X		X	X	
Pain score	X		X		X	X	
Overall survival			X	X	X	X	X

*FU* Follow up, *DGE* delayed gastric emptying

^a^Secondary outcomes include major and minor postoperative complication rates, in-hospital mortality, adverse events during gastroscopy, length of ICU, and hospital stay

### Data analysis

The statistical analysis will be performed using the statistical program SPSS (IBM). Both an intention-to-treat analysis and per-protocol analysis are planned. Primary and secondary outcomes will be compared using the chi-squared test, Fisher exact test for categorical variables, and Mann–Whitney *U* test for non-parametric variables. Mortality will be compared using Kaplan–Meier curves and log-rank test. The pain scales will be analyzed using mixed linear models, quality of life by using an analysis of covariance.

There will be an interim analysis after 75% of the participants were monitored for the occurrence of the primary endpoint. If the hypothesis is confirmed or reaching statistical significance is impossible at that point, the study will be ended.

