### Study design

The PROPPER trial is a multicenter, two parallel-group randomized controlled clinical superiority trial. The “Standard Protocol Items: Recommendations for Interventional Trials” (SPIRIT) 2013 statement was used to structure the design of this study [15] (Appendix 1). The study will be conducted in three tertiary referral clinics and university hospitals carrying out esophageal cancer resections:Department of General, Visceral, and Transplantation Surgery, University Medical Center MainzDepartment of General, Visceral, and Transplant Surgery, University Hospital Tübingen, Center for Esophageal DiseasesDepartment of Surgical, Oncological, and Gastroenterological Sciences—University of Padova

Patients presenting with resectable esophageal cancer or cancer of the gastroesophageal junction are assessed for meeting the inclusion or exclusion criteria (Table 1). After counseling by a treating surgeon, written consent of all participating patients will be obtained.

**Table 1 Tab1:** Inclusion and exclusion criteria

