#### Randomization and blinding methods

Patients will be randomized at the outpatient department to either PDG or NPDG. Randomization is executed centrally by an online randomization program for each participating center by the responsible study nurse. The online randomization program can be accessed by all centers via a personal log in on a website (propper-trial.goip.de). It was set up by independent statisticians who did not participate in the trial. The program is designed to allow only a certain number of randomization processes. The study nurse executing the randomization will inform the executing endoscopist about the randomization status on the day of the intervention.

While patients are blinded to the intervention, medical personnel (surgeons, endoscopists) are not, due to safety reasons. If patients show any symptoms or change in their clinical course after endoscopy, the treating doctors and nurses should be aware if the pneumatic dilatation was performed. On the one hand, because the intervention itself could cause a complication such as bleeding or perforation; on the other hand, other symptoms could falsely be explained by a dilatation. Therefore, we decided to unblind all treating personnel. However, the study nurses that will collect the outcomes from the patients and are responsible for data acquisition are unaware of the randomization status.

If any unintentional unblinding occurs, the study coordinator will be contacted.

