#### Sample size calculation

The hypothesis of this study is a lower rate of pyloric dysfunction in patients receiving preoperative EPBD compared to a control group receiving a sham intervention. In order to assess a sample size, the rates of pyloric dysfunction of the retrospective study of Hadzijusufovic et al. were used, since operative techniques and perioperative treatment pathways do not differ from those used in the PROPPER trial. In this study, the pyloric dysfunction rate in the PDG was 24.3% lower than in the NPDG (13.2% vs. 37.5%). With a two-sided 5% significance level, 49 patients per arm will be needed to achieve a power of 0.8 to detect a difference. Compensating for a dropout rate of approximately 20%, a sample size of 118 patients with 59 patients in every study arm will be needed. After 89 patients, an interim analysis will be carried out. The study will be terminated if the superiority of the EPBD intervention has already been proven or cannot be proven at all. Otherwise, recruitment will be carried on until 118 patients are included. This will be decided by the principal investigator (PI).

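### Two tests are named for the single primary comparison, only one of them fits the 49 per arm, and neither uses centre: naming one centre-stratified test would be a free improvement

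*Protocol article*

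**What the plan says.** The Data analysis section covers all categorical outcomes, primary and secondary, in one sentence: "Primary and secondary outcomes will be compared using the chi-squared test, Fisher exact test for categorical variables". It does not say which test is used for the primary endpoint, under what condition the other replaces it, or whether a continuity correction applies. Centre does not appear in it.

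The Sample size calculation takes 13.2% and 37.5% from the retrospective study and states "With a two-sided 5% significance level, 49 patients per arm will be needed to achieve a power of 0.8 to detect a difference". It names no test. It continues: "Compensating for a dropout rate of approximately 20%, a sample size of 118 patients with 59 patients in every study arm will be needed".

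On centres, Study design says "The study will be conducted in three tertiary referral clinics and university hospitals carrying out esophageal cancer resections", and Randomization and blinding methods says "Randomization is executed centrally by an online randomization program for each participating center by the responsible study nurse". Stratification by centre is a likely reading of that sentence, but the word is not used.

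The section on exclusions puts first an intention-to-treat analysis of all randomised patients, then a modified per-protocol analysis without three groups of patients.

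**The concern.** For one 2×2 table of this size, the uncorrected chi-squared test and Fisher's exact test do not give the same p-value, and they can fall on opposite sides of 0.05. If the choice is open when the data are seen, a borderline result can turn on it. The same holds at the interim analysis at 75% of participants, where the trial may end if the hypothesis is confirmed.

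The power statement also depends on the test. A sample size derived for an uncorrected test does not carry over to Fisher's test, which is conservative.

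Centre is a separate matter. If randomisation is balanced within centres and centres differ in event rate, a pooled test overstates the variance of the treatment difference and becomes conservative.

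**Working it through.** **Inputs.** From the Sample size calculation: p1 = 0.375 (control), p2 = 0.132 (dilatation), two-sided alpha 0.05, power 0.80, 1:1 allocation, 49 per arm raised to 59. Three centres from Study design. The article gives no event rates by centre, so those below are assumptions.

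**1. Reproducing the 49.** With the pooled variance under the null and no continuity correction, the mean rate is 0.2535 and

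n = [1.960·√(2·0.2535·0.7465) + 0.8416·√(0.375·0.625 + 0.132·0.868)]² / 0.243² = (1.2058 + 0.4972)² / 0.05905 = 49.1.

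Power at n = 49 by the same formula is 79.9%, so the stated figure reproduces. Two other uncorrected formulas give 46.4 (unpooled) and 47.6 (arcsine). The continuity-corrected formula gives (49.1/4)·[1 + √(1 + 4/(49.1·0.243))]² = 57.0, or 58 after rounding up. The 49 thus belongs to the uncorrected family.

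**2. Exact power.** All 2×2 tables were enumerated under binomial sampling at 37.5% vs 13.2%, and the probabilities of those with p ≤ 0.05 were summed.

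| Evaluable per arm | Chi-squared, uncorrected | Chi-squared, corrected | Fisher |
|---|---|---|---|
| 47 (59 × 0.8 = 47.2) | 79.1% | 71.8% | 71.9% |
| 49 | 81.0% | 74.3% | 74.3% |
| 59 (nobody lost) | 88.0% | 82.3% | 82.4% |

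Fisher reaches 80% at 56 per arm (80.6%; at 55 it has 79.6%). With 49 per arm and a common rate of 25%, actual type I error is 5.0% for chi-squared and 3.0% for Fisher.

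**3. How often the choice decides the result.** At 49 per arm and the planned rates the two tests disagree in 81.0 − 74.3, about 6.6% of trials before rounding. Example: 16 vs 7 events. The uncorrected statistic is 98·(16·42 − 33·7)² / (49·49·23·75) = 4.60, p = 0.032. Fisher gives p = 0.055.

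**4. Centre.** Trials were simulated (200,000 per scenario) with three near-equal centres and a constant odds ratio of (0.132/0.868)/(0.375/0.625) = 0.253. The pooled uncorrected chi-squared was compared with the uncorrected Cochran-Mantel-Haenszel (CMH) test. Each cell shows pooled / CMH.

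| Assumed control rates | Power, 49 per arm | Power, 59 per arm | Type I error, 49 per arm |
|---|---|---|---|
| 37.5% in all | 81.0 / 81.0% | 88.1 / 87.5% | 4.8 / 4.9% |
| 30, 37.5, 45% | 80.2 / 80.5% | 87.5 / 87.2% | 4.6 / 4.8% |
| 20, 37.5, 55% | 76.7 / 78.7% | 84.8 / 85.9% | 3.9 / 4.9% |
| 15, 37.5, 60% | 73.8 / 77.4% | 82.3 / 84.7% | 3.3 / 5.1% |

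With similar centres, stratifying changes power by about half a point at most, in either direction. With widely differing centres it gains between 85.9 − 84.8 = 1.1 and 77.4 − 73.8 = 3.6 points and brings type I error back to about 5%.

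**The case against.** Several points on the other side stand.

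- **The first-listed analysis is intention-to-treat.** It includes all randomised patients. With 59 per arm and no missing outcomes, even Fisher keeps 82.4%. A reader might infer that the trial has only 74% power. The article does not support that: the figure applies to 49 evaluable per arm and only under a conservative test.
- **Common practice would probably select chi-squared.** The smallest expected count at 49 per arm is 0.2535 × 49, about 12, well above the usual threshold of 5. That convention is an assumption here, since the article states no rule.
- **The retrospective p-value shows little.** Its p = 0.014 matches Fisher (0.0141) or the corrected chi-squared (0.0145) on the back-calculated counts 12/91 vs 9/24, and not the uncorrected test (0.0061). A reader might infer that this trial will use Fisher too. But the smallest expected count there is 24 × 21/115 = 4.4, so the same convention would have led to Fisher in that study and to chi-squared in this one.
- **Separate randomisation by centre is not stated outright.** The sentence may only mean that every centre uses the central program. The article also describes shared surgical training and homogeneous pathways, which argues against very different centre rates. Ignoring centre errs on the conservative side, so a positive result would stay valid.
- **Detail may sit in an analysis plan that is not shown.** This carries weight for centre adjustment, whose absence from a condensed article is not an error. It carries less for the test itself, because the article does not defer that choice: it names two tests beside a sample size that fits one.

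**Conclusion.** The point holds in a limited form. Two tests are named for one primary table without a rule, and the stated 80% power at 49 per arm is met only by the uncorrected one (81.0%, against 74.3%). The shortfall appears only if Fisher or a continuity correction is used together with the planned losses, or in the modified per-protocol set. At the full 59 per arm every version exceeds 80%.

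The fall to 74% comes entirely from the choice of test and has nothing to do with centre. The centre effect is separate and conditional: negligible if rates are similar, and about 1–4 points of power with type I error of about 3–4% if they differ as widely as assumed above.

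Severity is low. Fixing one test is a free improvement that removes an avoidable choice.

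**What to change.** Replace the shared sentence, for the primary endpoint, with one that names a single test: the Cochran-Mantel-Haenszel test stratified by centre, two-sided 5%, without continuity correction, reported with the centre-stratified risk difference and its 95% confidence interval. State that the same test applies in the intention-to-treat and modified per-protocol sets and at the interim look. Keep Fisher's exact test for rare secondary events. State in the randomisation section whether allocation is stratified by centre.

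In the Sample size calculation, add that the 49 per arm refers to an uncorrected test. If Fisher's test were preferred instead, about 56 evaluable per arm would be needed, which is 56/0.8 = 70 randomised per arm, or 140 in total.

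The recommended change costs a few sentences and needs no more patients or data. If centres turn out alike, the price is at most about half a point of power.

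### The plan allows a superiority stop at 89 of 118 patients but states no interim or final boundary; with p<0.05 at both looks and the uncorrected chi-squared test, the two-sided 5% level is not held

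*Protocol article*

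**What the plan says.** Two sections of the protocol article describe the same interim look.

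- **Sample size calculation:** "With a two-sided 5% significance level, 49 patients per arm will be needed to achieve a power of 0.8 to detect a difference". The total is then raised to 118 (59 per arm) for dropout. On the interim: "After 89 patients, an interim analysis will be carried out", and "The study will be terminated if the superiority of the EPBD intervention has already been proven or cannot be proven at all". Otherwise recruitment goes on to 118. The decision is given to the principal investigator.
- **Data analysis:** the look comes once 75% of participants have been monitored for the primary endpoint. "If the hypothesis is confirmed or reaching statistical significance is impossible at that point, the study will be ended". The chi-squared test and Fisher's exact test are both listed for categorical outcomes, and neither is assigned to the primary endpoint.

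The two timings agree: 0.75 × 118 = 88.5, which rounds up to 89. Two-sided 5% is the only significance level stated for the trial's hypothesis. Neither section gives an interim critical value, a spending function or a reduced final level.

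**The concern.** A trial that may declare success at an interim look, and if not may declare it at the end, has two chances of a false positive. If each chance uses the full 5%, the overall error exceeds 5% unless the test itself is conservative. The article leaves none of the rest of the rule open: it gives the timing, both reasons for stopping, what happens otherwise and who decides. It omits the one element that protects the stated level.

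At stake is the confirmatory claim on the primary endpoint. A boundary chosen after the interim data have been seen could not credibly restore the level.

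A secondary matter is who knows the interim result. The principal investigator decides on stopping, and the section on randomization and blinding says that treating personnel are unblinded.

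**Working it through.** **Inputs.** From Sample size calculation: two-sided 5%, power 0.80, rates 13.2% (EPBD) and 37.5% (control), 59 per arm, look at 89 of 118. From Data analysis: chi-squared or Fisher's exact test.

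**1. The plan's own figure.** For two proportions with pooled variance and no continuity correction:

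n = [1.960·√(2p̄(1−p̄)) + 0.842·√(p₁(1−p₁) + p₂(1−p₂))]² / (p₁−p₂)²

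With p₁ = 0.375, p₂ = 0.132 and p̄ = 0.2535, n = (1.206 + 0.497)² / 0.0590 = 49.1 per arm. Power at 49 is 0.799. The continuity-corrected formula needs 58 per arm. So 49 matches the uncorrected chi-squared test at a full 5%, with nothing set aside for an interim look. The 59 is 49 × 1.2 = 58.8, rounded up.

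**2. Normal theory, p<0.05 at both looks.** The information fraction is 89/118 = 0.754, so the two test statistics have correlation √0.754 = 0.868.

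- Stop in either direction: P(|Z₁|>1.96 or |Z₂|>1.96) = 0.0732.
- Interim stop for benefit only, final test two-sided: 0.0616. The chance of falsely claiming benefit rises from 0.025 to 0.0366.

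**3. Exact binomial enumeration.** Interim with 44 EPBD and 45 control patients, then 59 and 59, p<0.05 at both looks, equal true rates in the two arms:

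| Common event rate | Chi-squared, either direction stops | Chi-squared, only benefit stops | Fisher, either direction stops | Fisher, only benefit stops |
|---|---|---|---|---|
| 13.2% | 7.5% | 6.3% | 4.5% | 3.2% |
| 20% | 7.6% | 6.5% | 4.7% | 3.5% |
| 25% | 7.6% | 6.4% | 4.9% | 3.7% |
| 30% | 7.6% | 6.4% | 5.3% | 4.1% |
| 37.5% | 7.4% | 6.1% | 5.3% | 4.2% |

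A single final chi-squared test has an exact error of 4.9–5.3% over these rates, so the excess comes from the second look and not from the test.

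**4. Boundaries that hold 5% with a look at 89/118 (normal theory).**

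| Boundary | Interim p | Final p |
|---|---|---|
| Lan-DeMets, O'Brien-Fleming type | 0.0197 | 0.0441 |
| O'Brien-Fleming | 0.0203 | 0.0438 |
| Pocock | 0.0336 | 0.0336 |
| Haybittle-Peto | 0.001 | 0.05 |

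With the first pair, the exact chi-squared error over the same rates is 5.0–5.2%.

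**5. Power at 13.2% versus 37.5%, chi-squared, exact, 59 per arm.**

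| Plan | Power | Chance of stopping at 89 |
|---|---|---|
| Two looks, p<0.05 at each | 0.896 | 0.78 |
| Two looks, Lan-DeMets limits | 0.873 | 0.63 |
| Single look at 118 | 0.880 | – |

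**The case against.** Four points can be made in defence of the plan.

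- **No sentence says that p<0.05 applies at the interim.** The protocol speaks of superiority being proven or the hypothesis confirmed, and an analysis plan that is not shown could define those words. This stands as a limit on the claim: the inflated rates are conditional. It does not remove the point, because the article sets out the stopping rule and the 5% level together and gives no other level.
- **A reader might infer that the trial's error rate simply is about 7.5%.** The documents do not support that. The figure needs the uncorrected chi-squared test and a stop in either direction. The Sample size section words the stop as superiority of EPBD, and a benefit-only stop gives 6.1–6.5%.
- **Fisher's exact test, also named, roughly holds 5% at two unadjusted looks.** This is true, but the protection comes from that test's conservatism and not from a plan. It is also not the test that the sample size matches.
- **A reader might infer that the principal investigator sees the comparative results, and that feeding of the last 29 patients (118 − 89) is open to bias.** The protocol says only that this person decides; it does not say who runs the look or who sees the comparison. Patients and the nurses collecting outcomes are blinded, feeding follows a routine common to both groups, and defined vomiting triggers endoscopy and EPBD in all centers. Some discretion does remain, since an EPBD done for other reasons also counts as a primary event and treating personnel know the allocation.

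**Conclusion.** The point holds in conditional form. The protocol permits a superiority stop at 89 of 118 patients and a second test at 118, states only two-sided 5%, and gives no boundary. With p<0.05 at both looks:

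- uncorrected chi-squared, either direction stops: about 7.3–7.6%;
- uncorrected chi-squared, only benefit stops: about 6.1–6.5%;
- Fisher's exact test, under either stopping rule: about 3.2–5.3%.

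These figures assume null event rates between 13.2% and 37.5% and that all 118 patients are evaluable, with 89 of them at the interim. If 89 instead meant evaluable patients out of a final 98 (2 × 49), the fraction would be 0.91 and the normal-theory figure for a stop in either direction 6.4%. The size of the excess therefore depends on the test and on the direction of stopping. The absence of a stated boundary does not, and it should be settled before the interim look.

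**What to change.** 1. Name the single test used for the primary endpoint at both looks.
2. State a group-sequential boundary for the intention-to-treat primary comparison that holds two-sided 5% overall. One example is Lan-DeMets O'Brien-Fleming-type spending: stop for superiority at 89 patients only if p≤0.0197, and use p≤0.0441 at 118. O'Brien-Fleming or Haybittle-Peto limits would serve equally; what matters is that one is fixed in advance.
3. State who carries out the interim comparison, and that the principal investigator receives only a stop or continue recommendation.

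**Cost.** A few sentences in the protocol and no change to the planned 118. At 59 per arm with chi-squared, power falls by 2.3 points against the unadjusted two-look plan (0.896 − 0.873) and by 0.7 points against a single look (0.880 − 0.873). If dropout leaves 49 per arm (37 per arm at the interim), exact power under these limits is 0.801 with chi-squared, so the 0.80 target is still met; with Fisher's test it would be 0.733. The main price is that the chance of stopping early under the design effect falls from about 0.78 to 0.63.

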### Dissemination plans

The trial results will be presented at scientific conferences and published in appropriate medical journals. The present article is the trial protocol. Patients may request a summary of the trial results through the hospital website or directly from the study team.

